### Randomisation

Eligible participants, immediately after providing baseline assessment data, will be randomly assigned in a 1:1 ratio to the intervention or the control group according to a computer-generated random schedule in permuted blocks of six with no stratification. A statistician who is not involved in recruitment, treatment allocation, and outcome assessment will generate the randomisation numbers. The statistician will put the randomly sequenced numbers indicating group assignment into sealed, opaque, containing a carbon paper inside, and sequentially numbered, otherwise identical, envelopes. Upon enrolling each participant, a research assistant who is not involved in recruitment and outcome assessment will take an envelope consecutively, write the participant’s study identifier on the envelope, open it and inform the principal investigator about the treatment allocation.

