### Blinding

Due to the nature of the intervention, the participants and the principal investigator who delivers the self-management programme will not be blinded to treatment allocation. However the research assistants who will administer the outcome assessment, data entry and analysis will remain blinded to the treatment allocation. The research assistants will not be involved in implementing the programme or treatment of the participants at any stage. The participants will be asked not to tell the research assistants about their treatment allocation. However the research assistants who will collect the participants’ feedback on usefulness of the programme will not be blinded to treatment allocation as they need to know this information for conducting the assessment.

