### Data collection procedures

All potential participants will be identified by reviewing their medical records or referrals by stroke nurses at the study venues. The principal investigator or research assistants will screen the participants in a face-to-face interview for their eligibility and willingness to participate in the study. Written informed consent will be obtained from those who are eligible. A card indicating participants’ involvement in the study and means of urgent contact will be provided to each participant after obtaining the consent. The consented participants’ demographic and clinical information will be retrieved from their medical records. Baseline and follow-up assessments will be conducted by two research assistants. The participants will be scheduled via phone by a research assistant for baseline assessment within one month after their discharge from hospital. Immediately after baseline assessment is completed, the participants will be randomly assigned to either the intervention or the control group. At 8 weeks after randomisation, the participants will be scheduled via phone by the research assistant again for follow-up assessment. The research assistants will administer the assessment tools in a face-to-face interview at the participants’ homes. The administration of the questionnaires has been pilot tested among six Chinese community-dwelling stroke survivors (mean age 55 years, SD 10.35, range 35–64 years). It took an average of one hour to complete the six questionnaires. Another research assistant will call the participants in the intervention and control groups at the time immediately after programme completion to collect their feedback on the programme (Table 3). The research assistants will be trained to administer the assessment tools consistently and non-judgmentally; and be reminded of the importance of confidentiality and safe storage of data. Inter-rater reliability between research assistants will be checked using Kappa statistics before data collection.

**Table 3 Tab3:** Summary of measurements and study outcomes

Measurements	Instruments	Group	Baseline	Follow-up	Outcomes	
					1°	2°
Self-efficacy	SSEQ	IG, UG	×	×	×	
Outcome expectation	SSOES	IG, UG	×	×	×	
Satisfaction with performance of SSMB	SSBPS	IG, UG	×	×		×
Health-related quality of life	SSQOL	IG, UG	×	×		×
Depressive symptoms	GDS	IG, UG	×	×		×
Community reintegration	RNLI	IG, UG	×	×		×

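### The unblinded principal investigator is told every allocation from a list in fixed blocks of six and may also screen, so allocations are partly predictable if the block size is known

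*Protocol article*

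**What the plan says.** **Sequence.** The Randomisation section of the protocol article specifies a "computer-generated random schedule in permuted blocks of six with no stratification". Participants, "immediately after providing baseline assessment data, will be randomly assigned in a 1:1 ratio", so one sequence serves all three hospitals named under Study design and setting.

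**Separation of roles.** The same section states that "A statistician who is not involved in recruitment, treatment allocation, and outcome assessment will generate the randomisation numbers". Envelopes are sealed, opaque, carbon-lined and numbered in order. At enrolment "a research assistant who is not involved in recruitment and outcome assessment will take an envelope consecutively", writes the study identifier on it, and is then to "open it and inform the principal investigator about the treatment allocation".

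**The principal investigator.** Under Blinding, "the principal investigator who delivers the self-management programme will not be blinded to treatment allocation". Under Data collection procedures, "The principal investigator or research assistants will screen the participants in a face-to-face interview for their eligibility and willingness to participate in the study".

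**Timing.** Under Participants, eligibility requires that discharge home is expected within seven days. Under Data collection procedures, a research assistant books the baseline visit by telephone, to take place within a month of discharge. Randomisation follows that visit.

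**The concern.** The Randomisation section keeps the statistician and the envelope opener out of recruitment. It sets no such limit on the principal investigator, who is told every result, and Data collection procedures lets that person screen. Because the list is unstratified, the principal investigator sees the whole running sequence rather than one site's part of it.

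Sealed envelopes conceal each single assignment. They do not stop inference from earlier assignments when every block holds exactly three of each arm. Some screening judgements leave room for discretion: willingness, ability to attend the sessions, and limited comprehension. If a guess about the coming arm influences such a judgement, the arms can differ in ways that adjustment for measured covariates does not remove. The primary outcome is self-reported confidence in participants who know their arm, so the trial should not add an avoidable source of bias.

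**Working it through.** **Inputs.** Block size 6, ratio 1:1, no stratification (Randomisation). Total 160 in 12 months (Sample size estimation). Discharge within 7 days of screening (Participants) and baseline within one month of discharge (Data collection procedures), taken as 7 + 30 = 37 days at most.

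**1. The plan's own figure.** The article gives no figure for predictability. Its sample size reproduces: a two-sided t-test with effect size 0.5, alpha 0.05 and power 0.80 needs 63.8, so 64 per group. Then 64 / 0.81 = 79.01, rounded up to 80 per group, or 160. This total is used below only for the accrual rate.

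**2. The next envelope.** Take an observer who knows the block size and all earlier allocations. With a and b places left for the two arms in the current block, the best guess is right with probability max(a, b) / (a + b). Averaging over all C(6,3) = 20 arrangements gives:

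| Place in block | 1 | 2 | 3 | 4 | 5 | 6 |
|---|---|---|---|---|---|---|
| Guess correct | 0.5 | 0.6 | 0.6 | 0.7 | 0.7 | 1.0 |
| Certain | 0 | 0 | 0 | 0.1 | 0.4 | 1.0 |

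- Correct: 0.5 + 0.6 + 0.6 + 0.7 + 0.7 + 1.0 = 4.1 of 6 = 68.3%.
- Certain: 0.1 + 0.4 + 1.0 = 1.5 of 6 = 25%.
- Over the 26 complete blocks in 160: 26 x 1.5 = 39 certain allocations, and 26 x 4.1 = 106.6 of 156 guessed correctly.

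**3. At screening.** Suppose k other randomisations, in known order, will come before the person being screened. The observer then lacks the last k results before that person's place. For k = 1, the guess probabilities by place become 0.5, 0.5, 0.6, 0.6, 0.7, 0.7, which sum to 3.6, and 3.6 / 6 = 60.0%. Certainty is (0.1 + 0.4) / 6 = 8.3%. In the same way:

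| Pending (k) | 0 | 1 | 2 | 3 | 4 | 5 or more |
|---|---|---|---|---|---|---|
| Guess correct | 68.3% | 60.0% | 56.7% | 53.3% | 51.7% | 50% |
| Certain | 25% | 8.3% | 1.7% | 0 | 0 | 0 |

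**4. How many are pending.** Assuming even accrual, 160 / 52 = 3.1 randomisations per week. Five take 5 / 3.1 = 1.6 weeks, about 11 days. The longest lag spans 160 / 365 x 37 = 16.2 randomisations. The article sets only an upper limit on the lag, so short queues can occur, for example early in recruitment.

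**5. Randomly varying block sizes.** This was simulated over 160 allocations for a best guesser who sees every allocation and knows only the set of sizes. The sets are illustrative assumptions.

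| Block sizes | Certain | Next guess correct |
|---|---|---|
| 6 only | 24.4% | 68.2% |
| 4, 6 | 5.4% | 69.3% |
| 4, 6, 8 | 2.5% | 67.9% |
| 2, 4, 6, 8 | 1.9% | 68.7% |

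The first row differs slightly from step 2 because 160 is 26 blocks plus 4. Varying the sizes removes most certain predictions but does not reduce better-than-chance guessing.

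**The case against.** The strongest reply is that 25% and 68% describe a decision the principal investigator is not said to make. The stated role is screening in hospital, whereas the order of randomisation depends on when participants from three hospitals complete home visits that research assistants book and conduct. That makes a person's place in the list hard to know at screening, and the figures in step 3 are themselves generous because they assume the order is known. **This stands**, and it is why the next-envelope figures cannot serve as the size of the problem at screening.

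Prediction also requires knowledge of the block size. The article does not say that the principal investigator knew it, nor that it was withheld. A reader might infer from its appearance in print that recruiters knew it. The documents do not support that: registration was in April 2014 and publication in August 2016, and nothing shows whether enrolment was still open then.

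There are real safeguards: an independent statistician, carbon-lined envelopes marked before opening, an envelope opener outside recruitment, and blinded outcome assessors. Most eligibility criteria are objective. The planned models use baseline scores and adjust for listed covariates that look unbalanced. This limits bias from measured prognosis, but not from unmeasured prognosis.

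Fixed blocks with concealed envelopes are a recognised choice, and the text contains no contradiction. What the reply leaves unanswered is that the one person who sees the whole sequence is also allowed to screen.

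**Conclusion.** The point holds as a minor design weakness. If the principal investigator knows the block size, 25% of next allocations are certain and 68% can be guessed. At screening, the advantage is 60% correct with one randomisation pending and none with five or more. The route is open mainly when the queue is short, or if the principal investigator could influence who reaches baseline and when; the article describes no such influence.

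Two stronger readings go too far. A reader might infer that allocation concealment fails. It does not: each envelope is adequately concealed, and the weakness is inference from past results. A reader might also infer that about two thirds of allocations are foreseeable when patients are recruited. The gap of days to weeks between screening and randomisation rules that out as a general statement. Whether any bias arises, and how large it would be, cannot be worked out from the document.

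The conclusion assumes that the block size is known, that every past allocation is remembered, and, for the queue lengths, that accrual is even.

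**What to change.** **Main change (Data collection procedures).** State that only research assistants who do not see allocations will screen and take consent, and that the principal investigator has no part in deciding who proceeds to baseline or when. Research assistants already share the screening task, so no new staff are needed. The assistant who opens envelopes is already outside recruitment; the one who collects programme feedback is unblinded and should not screen either.

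**Supporting change (Randomisation).** Have the independent statistician draw up the list with randomly varying block sizes, and state that the sizes are not disclosed to trial staff. This alone is not enough, as step 5 shows.

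**Cost.** One new list and a sentence in each section, with less flexibility over who screens. Two fixed blocks of six supply exactly the six intervention participants that start a programme run, so with varying sizes the runs may fill slightly less regularly. The sample size is unaffected.

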### Blinding

Due to the nature of the intervention, the participants and the principal investigator who delivers the self-management programme will not be blinded to treatment allocation. However the research assistants who will administer the outcome assessment, data entry and analysis will remain blinded to the treatment allocation. The research assistants will not be involved in implementing the programme or treatment of the participants at any stage. The participants will be asked not to tell the research assistants about their treatment allocation. However the research assistants who will collect the participants’ feedback on usefulness of the programme will not be blinded to treatment allocation as they need to know this information for conducting the assessment.

### Intervention

#### Intervention group: a nurse-led community-based self-management programme

Participants assigned to the intervention group will receive a 4-week nurse-led community-based self-management programme in addition to usual care. The programme is aimed at enhancing community-residing stroke survivors’ capabilities in self-managing their post-stroke health conditions. It includes one 1.5-hour individual home visit, two 1.5-hour group sessions held in a community centre, and three follow-up phone-calls (Table 1). The programme is underpinned by Bandura’s constructs of self-efficacy and outcome expectation [16]. The programme will be delivered by the principal investigator who is a registered nurse experienced in stroke care and chronic disease management. Each participant will receive a programme booklet and two DVDs specifically designed for this programme. The booklet provides information about stroke recovery and self-management, and records participants’ goals and action plans. The DVDs contain video clips of experience sharing by 15 stroke survivors who have successfully managed their stroke. A panel of experts including two nurse academics, two advanced practice nurses, one nurse manager and one physician who are experienced in stroke care has reviewed the programme contents and the booklet. A protocol detailing the programme contents and delivery methods have been developed to ensure consistent delivery of the programme. The programme will commence when six participants have been assigned to the intervention group and repeated to accommodate all participants assigned to this band. Family members or informal carers of each participant who are interested may join the programme as an accompanying person.

**Table 1 Tab1:** Overview of the nurse-led community-based self-management programme for community-residing stroke survivors

Week	Programme components	Key contents
1	Home visit (at participant’s home)	- Perform an individualised assessment. - Provide information about stroke self-management. - Establish a short-term goal and an action plan. - Video viewing.
2	Group sessions (in a community centre)	- Discuss the physical and psychosocial consequences of stroke. - Discuss the practical tips of managing post-stroke challenges. - Facilitate reflection and experience sharing among the group. - Explore alternative ways to better implement the action plans. - Practice the use of core self-management skills. - Video viewing.
3 & 4	Three follow-up phone calls	- Review progress towards goal attainment. - Provide individualised feedback and positive reinforcement. - Encourage to continue, revise, or set a new short-term goal.

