### Sample size estimation

Primary outcome of this trial is stroke survivors’ self-efficacy in performing self-management behaviours measured by the Stroke Self-Efficacy Questionnaire at eight weeks after randomisation. A sample size of 64 per group (128 for two groups) is required to detect a significant mean difference in self-efficacy between groups for a medium effect size of 0.5 [14] with significance set at 0.05 and a power of 0.8 [15]. Taking into consideration an attrition rate of 19 % over six months among stroke survivors [14], the final sample size is 160 (80 participants per group). Recruitment of participants is anticipated to take 12 months.

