### Programme contents

The nurse will schedule with the participants for home visit. During home visit, the nurse will assess the participant’s current medical, emotional and role management of their post-stroke conditions [4, 8], and their self-efficacy and outcome expectancy beliefs of performing self-management behaviours. Based on the assessment, the nurse will work with the participant to establish a short-term goal of importance to stroke recovery, and develop a realistic action plan to achieve the goal [4]. Information about stroke self-management and core self-management skills such as problem-solving and decision-making will be provided. Furthermore participants will be guided to view one to two video clips on the DVDs to enable them to learn from other stroke survivors’ experiences. Positive reinforcement will be provided to promote their confidence in implementing their action plans [16]. Participants will be encouraged to view the videos, read the programme booklet, and record the implementation of their action plans after the home visit.

In the following week after the home visit, two group sessions will be held on the same day in a community centre. During the group sessions, participants will be provided with information about the physical and psychosocial consequences of stroke, and practical tips for effective stroke self-management. More importantly, the nurse will act as a facilitator to encourage participants to reflect and share their barriers to and facilitators of implementing their action plans. Based on the common problems among the group, video clips of sharing by stroke survivors will be presented. Participants will be facilitated to explore own ways to address their barriers. Examples will be provided to guide their practice of core self-management skills to better implement their plans. If necessary, their action plans will be revised. Positive reinforcement will be provided and participants are encouraged to visualise their expected positive outcomes after performing the self-management behaviours [16]. Participants will be encouraged to continue implement their action plans and record their progress after the sessions.

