### Statistical analysis

Statistical analyses will be performed using the IBM SPSS Statistics version 22 (SPSS Inc., Chicago, IL, USA). All primary analyses will be conducted on an intention-to-treat basis. No interim analyses will be undertaken. Descriptive statistics will be used to summarise participants’ baseline characteristics and outcome variables. All continuous outcomes will be assessed for normality in distribution. Appropriate transformation of skewed data will be performed before analysis. Chi-square tests and independent t-tests will be used to compare the demographic and clinical characteristics, and mean scores of outcomes between the intervention and control groups at baseline. A generalised estimating equation (GEE) model will be employed to assess differential change of the primary and secondary outcomes across the time points (baseline and eight weeks after randomisation) between the two groups. Adjustment will be made for potential confounding demographic and clinical variables, including gender, age, number of strokes, NIHSS, and the Barthel ADL Index, that were ‘unbalanced’ between the two groups (*p* < 0.25) [31, 32]. The longitudinal association of self-efficacy and outcome expectation with secondary outcomes will be examined using GEE model. GEE model can account for intra-correlated repeated measures data and accommodate missing data caused by dropouts, provided the data are missing at random [33], and is particularly suitable for intention-to-treat analysis without imputation for missing data. Significance level will be set at two-sided *p* < 0.05 and all statistical tests will be two-tailed.

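### The intervention is delivered in runs of six, but neither the sample size nor the GEE as described allows for correlation within a run, so standard errors are too small for any positive within-run ICC

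*Protocol article*

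**What the plan says.** **Delivery.** The protocol's Intervention section lists the components: "It includes one 1.5-hour individual home visit, two 1.5-hour group sessions held in a community centre, and three follow-up phone-calls". A later sentence there says that a run begins when six people have been assigned to the intervention, and that runs repeat until everyone in the arm has been served. Under Programme contents, both group sessions fall on one day, and "the nurse will act as a facilitator to encourage participants to reflect and share their barriers". The video clips shown depend on the problems that the group has in common. Table 2 lists experience sharing in the group as one route to self-efficacy, which is the primary outcome. The Control group section gives usual care only, with no groups.

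**Sample size.** Sample size estimation says: "A sample size of 64 per group (128 for two groups) is required to detect a significant mean difference", with an effect size of 0.5, significance 0.05 and power 0.8. The only inflation is for loss: "Taking into consideration an attrition rate of 19 % over six months among stroke survivors", after which "the final sample size is 160 (80 participants per group".

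**Analysis.** Statistical analysis compares change between the arms from baseline to eight weeks. The correlation that it names is that of repeated measurements: "GEE model can account for intra-correlated repeated measures data". Programme run appears neither there nor among the adjustment variables.

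**The concern.** Participants are randomised individually, but those in one arm are then treated together. This is a partially nested design. If members of a run influence one another, as the programme's own theory intends, their outcomes at eight weeks are positively correlated. The mean of the intervention arm then varies more than the same number of independent people would suggest. Robust GEE errors clustered on the participant do not pick this up, because the extra correlation is between participants.

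The test of the primary outcome would then reject too often under the null, and its confidence interval would be too narrow. The error favours the intervention. If the analysis is corrected, the type I error is restored, but the planned number buys less power than stated.

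**Working it through.** **Inputs from the protocol:** standardised difference 0.5; two-sided 5% ("all statistical tests will be two-tailed"); 64 evaluable and 80 recruited per arm; 19% attrition; runs of six. **Assumed, because the documents give no value:** within-run ICC of 0.02, 0.05 or 0.10.

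**Step 1. Reproduce the plan's figure.** An independent two-sample t-test with 64 per arm and d = 0.5 has noncentrality 0.5/√(2/64) = 2.828 and power 80.1%; 63 per arm gives 79.5%. Then 64/0.81 = 79.01, rounded up to 80 per arm, 160 in all. The stated number is fully accounted for with no design effect.

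**Step 2. Run size.** 80/6 is about 13 runs. After 19% loss, 6 × 0.81 = 4.86 are analysed per run. Both m = 4.86 and m = 6 are carried forward.

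**Step 3. Variance.** Design effect in the intervention arm: DE = 1 + (m − 1) × ICC. Variance of the difference between arms relative to independence: (DE + 1)/2. The true standard error exceeds the planned one by the square root of that.

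**Step 4. Type I error of the uncorrected test.** 2 × [1 − Φ(1.96/√((DE + 1)/2))]. For m = 6 and ICC 0.05: DE = 1.25, variance ratio 1.125, standard error ratio 1.061, so 2 × [1 − Φ(1.848)] = 6.5%.

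**Step 5. Power of a corrected test.** Noncentral t with 64 per arm, total SD 1 in each arm, and standard error √(DE/64 + 1/64). The Satterthwaite degrees of freedom use 64/m runs in the intervention arm.

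| ICC | m | DE | SE ratio | Type I error, uncorrected test | Power, corrected SE, 126 df | Power, corrected SE, Satterthwaite df |
|---|---|---|---|---|---|---|
| 0.02 | 4.86 | 1.077 | 1.019 | 5.5% | 78.6% | 77.2% |
| 0.02 | 6 | 1.100 | 1.025 | 5.6% | 78.2% | 76.3% |
| 0.05 | 4.86 | 1.193 | 1.047 | 6.1% | 76.4% | 74.8% |
| 0.05 | 6 | 1.250 | 1.061 | 6.5% | 75.4% | 73.1% |
| 0.10 | 4.86 | 1.386 | 1.092 | 7.3% | 72.9% | 71.0% |
| 0.10 | 6 | 1.500 | 1.118 | 8.0% | 70.9% | 68.2% |

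Part of the loss in the last column comes from the degrees of freedom alone: at ICC 0 that test has 78.9% (m = 4.86) or 78.4% (m = 6).

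**Step 6. Power of the uncorrected test.** Φ((2.828 − 1.96)/√((DE + 1)/2)). At ICC 0.05 this is 79.7% for m = 4.86 and 79.4% for m = 6; at ICC 0.10 and m = 6 it is 78.1%. The uncorrected test therefore keeps nearly all its rejection rate. The inflated type I error and the power loss belong to two different tests.

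**The case against.** **The ICC is unknown and may be small.** This stands. One nurse delivers every run, so there is no variation between therapists. A written protocol is meant to keep delivery uniform. Group contact is two sessions on one day, while the home visit and calls are individual. At ICC 0 the stated 80% is right, and at 0.02 the type I error is only 5.5–5.6%. A reader might infer that the standard errors are known to be too small and the power known to be overstated. The documents do not support that: both need a positive ICC. The planned sharing makes one plausible, not certain.

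**Two harms at once.** A reader might also infer that the planned test suffers both an inflated type I error and a power in the low to mid 70s. It does not, as Step 6 shows. Without correction the error rate rises; with correction the power falls.

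**Baseline scores.** The power figures are for a follow-up-only comparison, whereas the GEE models change. This stands too. Suppose a within-person correlation of 0.6, with the run effect arising after baseline. A change score then has variance 2 × (1 − 0.6) = 0.8. At ICC 0.05 and m = 6, the variance of the difference is (0.8 + 5 × 0.05 + 0.8)/64 = 1.85/64, giving about 83% power with 126 df and 81% with Satterthwaite df. At a correlation of 0.5 there is no gain. The documents give no correlation, so power below 80% is not established for the planned model. The type I error is not rescued: in the same example the variance ratio is 1.85/1.6 = 1.156, slightly above the 1.125 of the follow-up comparison.

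**A condensed article.** A fuller analysis plan might name programme run. That limits the criticism of the GEE to what the article describes. It does not touch the sample size, which is a completed calculation.

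**Conclusion.** The point holds in conditional form. Group delivery in one arm, planned interaction aimed at the primary outcome, and a sample size with no allowance for it are all in the text. The one correlation that the analysis names is within the participant. Followed as written, the analysis gives standard errors that are too small for any positive within-run ICC. The type I error would be about 5.5–5.6%, 6.1–6.5% and 7.3–8.0% at assumed ICCs of 0.02, 0.05 and 0.10. These sizes rest on the assumed ICCs, on 4.9 to 6 analysed per run, and on equal total variance in the two arms. The direction does not depend on the chosen ICC, provided it is above zero. At the low end the effect is minor; at 0.05 or more it could matter for a borderline primary result.

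**What to change.** 1. Record the programme run of every intervention participant. It is known at delivery, and without it no correction is possible later.
2. In Statistical analysis, make run the clustering unit for the primary analysis. Either fit a run effect in the intervention arm only, or use robust errors clustered on run with each control as their own cluster. Use a small-sample correction in both cases, since there are only about 13 runs.
3. In Sample size estimation, state that 80% power assumes no within-run correlation. Add that, for a follow-up comparison with 64 per group and the corrected small-sample test, power is about 76–77%, 73–75% and 68–71% at ICCs of 0.02, 0.05 and 0.10, before any gain from baseline scores. Label the ICCs as assumptions.

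The cost is one identifier and one clustering term, slightly wider intervals, and a lower stated power. The delivery of the programme does not change.
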